### Results

All assessments will be conducted by a blinded evaluator. The volunteers will undergo initial evaluation, including medical history, gynecological examination, functional assessment of the PFM, and questionnaires. The assessments will take place at three time points: before treatment (baseline assessment), at the end (final assessment), and one month after the last session (re-assessment). Fig 7 illustrates the assessment and re-assessment items.

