### Sample size

The sample size was pre-determined using G-Power 3.1.9.2 (F-tests—ANOVA: repeated measures, between groups), based on a previous study [46] utilizing vaginal manometry data. The sample size was estimated with a significance level of 0.05, power of 98%, and effect size of 0.23. According to this methodology, the sample size resulted in 27 participants. An additional 20% for possible losses (5 volunteers) was added. Thus, 32 volunteers will be recruited and randomized into two groups of 16 participants each.

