### Randomization, allocation concealment, and blinding

The randomization process will be carried out electronically through the website http://www.randomization.com to assign each participant to the PFMT or CG. Allocation will be 1:1, and each participant will have an equal probability of belonging to either group. Two pieces of information will be entered: the sample size and the number of groups. Website will generate specific coding for each group and will distribute subjects randomly. To ensure blinding in this study, the processes of randomization, assessment/reassessment, training of selected volunteers, and data analysis will be performed by distinct researchers.

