### Statistical analysis

Data will be analyzed using the Statistical Package for Social Science (SPSS) version 22.0, and will be used Excel Software version 2019 to capture the data. Initial analysis will present sociodemographic and clinical parameters in descriptive tables showing mean values, standard deviation, frequency, medians, and percentiles. Additionally, 95% confidence intervals will be presented. To assess initial group differences, unpaired t-test or Mann-Whitney test will be used for continuous variables, and chi-square test for categorical variables. Depending on data normality, repeated measures ANOVA or Kruskal-Wallis test followed by Tukey post-test will identify differences. Time-group interaction and intra-group variations for studied variables will be analyzed. Mauchly test will check sphericity, and if violated, Greenhouse-Geisser correction will be applied. Effect size (Cohen’s f2) and statistical power will also be calculated. Significance level of 5% will be considered.

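### The Tukey post-test named after the repeated measures ANOVA does not fit a two-group, three-visit design: it cannot test the between-group difference in change, and over all six means one error term misjudges visit or group comparisons

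*Protocol article*

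**What the plan says.** The Statistical analysis section of the protocol article chooses the method by normality and then states that "repeated measures ANOVA or Kruskal-Wallis test followed by Tukey post-test will identify differences". On the natural reading Tukey follows both tests, so on the parametric branch it comes after the repeated measures ANOVA. It is the only follow-up procedure named.

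The same section adds: "Time-group interaction and intra-group variations for studied variables will be analyzed". On sphericity it says: "Mauchly test will check sphericity, and if violated, Greenhouse-Geisser correction will be applied". On the error rate: "Significance level of 5% will be considered".

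The design is described elsewhere. The Results section has three visits: "before treatment (baseline assessment), at the end (final assessment), and one month after the last session (re-assessment". The Sample size section has two arms: "32 volunteers will be recruited and randomized into two groups of 16 participants each".

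The text does not say which means Tukey compares (three visits, two groups or all six cells) or which error term it uses.

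**The concern.** A group-by-visit design contains two kinds of comparison. Visits are compared within the same women, whose measurements are correlated. Groups are compared between different women. The two need different standard errors, and one Tukey procedure with one error term cannot supply both.

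The treatment effect here is neither kind of pair. It is the difference between the groups in their change from baseline, which involves four means at a time. The time-group interaction test covers it overall. With three visits, however, that test has two degrees of freedom and does not show at which visit, or in which direction, the groups differ. The plan gives the task of locating differences to a procedure that cannot make this comparison.

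At stake is which visit and group differences are reported for manometry and the other scores.

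**Working it through.** **Inputs.** From the protocol: two groups, three visits, significance level 5%, and 27 women before the allowance for losses (Sample size). Assumed: a 14/13 split of those 27, SD 1, equal correlation ρ between visits, and ρ from 0.3 to 0.8, because the protocol gives no visit correlation. The protocol gives no figure for the post-test, so there is none to reproduce. The 27 is used only as a working size.

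**Step 1: the two variances.** With n women in a group:

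- change between two visits within a group: 2σ²(1−ρ)/n
- difference between groups at one visit: σ²(1/n₁ + 1/n₂)

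The pooled cell mean square estimates σ² on 27×3 − 6 = 75 degrees of freedom. The within-woman residual estimates σ²(1−ρ) on (27−2)×(3−1) = 50. Used for the wrong comparison, each distorts the standard error:

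| ρ | Pooled error overstates the SE of a visit change by 1/√(1−ρ) | Within-woman error shrinks the SE of a group difference to √(1−ρ) |
|---|---|---|
| 0.3 | 1.20 times | 0.84 |
| 0.5 | 1.41 times | 0.71 |
| 0.7 | 1.83 times | 0.55 |
| 0.8 | 2.24 times | 0.45 |

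**Step 2: the ways to apply the sentence.**

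- *Three visits within a group, within-woman error.* Simulated family-wise error is 4.8 to 5.1% for ρ from 0.3 to 0.9, so this is valid under sphericity. Under two assumed non-spherical patterns it is 5.5% and 6.2%, and about 6.5% when epsilon is about 0.64. Greenhouse-Geisser adjusts the F test and leaves these comparisons unchanged.
- *Two groups.* There is one pair, so Tukey adds nothing to the F test.
- *All six means.* There are 15 pairs: 6 compare visits within a group, 3 compare groups at the same visit, and 6 differ in both. None is the difference in change, (PFMT final − PFMT baseline) − (comparator final − comparator baseline).

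**Step 3: six means, pooled error.** The Tukey limit for six means on 75 degrees of freedom is |t| > 2.92. A 0.7 SD change in a group of 14 has expected t of 0.7/√(2/14) = 1.85, well short of the limit. A higher correlation narrows the spread around 1.85, so power falls as the data become more informative. Simulated power (20,000 to 40,000 trials per setting), beside paired t tests at 0.05/3:

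| ρ | 0.3 | 0.5 | 0.6 | 0.7 | 0.8 |
|---|---|---|---|---|---|
| Six-mean Tukey, pooled error | 11% | 8% | 7% | 5% | 3% |
| Paired, Bonferroni | 34% | 47% | 58% | 73% | 90% |

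Part of this gap is family size (15 pairs against 3). At ρ = 0.6, six-mean Tukey with the within-woman error has 50%. So of the 58 − 7 = 51 points, 50 − 7 = 43 come from the error term and about 8 from the larger family.

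A like-for-like comparison uses six-mean Tukey both times, 16 per group and a 0.8 SD change. Pooled error gives 23%, 20%, 15% and 13% at ρ = 0.3, 0.5, 0.7 and 0.8. Within-woman error gives 41%, 60%, 88% and 98%. At ρ = 0.3 the loss is (41 − 23)/41 = 44% of the power.

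**Step 4: six means, within-woman error, no true effect.** Share of trials with at least one false group difference at the three visits:

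| ρ | 0.3 | 0.5 | 0.6 | 0.7 | 0.8 |
|---|---|---|---|---|---|
| False group difference | 5% | 10% | 15% | 23% | 32% |

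With the pooled error the same rate is about 1.3%, so the inflation belongs to the within-woman error alone. Repeat runs of Steps 3 and 4 differ by about one point.

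**The case against.** The strongest defence is that the plan never says to run Tukey over six means or with one error term. An analyst who has just fitted a repeated measures ANOVA with a sphericity check would hardly discard its within-woman error. Visit is the only factor with more than two levels, and the plan announces changes within groups, so Tukey across three visits is a sensible reading. On that reading the error rate is about 5%. Power for the 0.7 SD change is 69%, 83% and 95% at ρ = 0.6, 0.7 and 0.8, which is better than the Bonferroni paired tests (58%, 73% and 90%). All of this stands.

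A reader might therefore infer too much in three ways. One is that the analysis as planned will lose most of its power or produce false group differences. The document does not support that, since it fixes neither a six-mean family nor an error term, and at ρ = 0.3 false group differences stay at about 5%. Another is that Tukey is invalid because the visits are correlated. It is not: equally correlated means with the within-woman error suffice. The third is that the treatment effect goes untested, but the time-group interaction is planned separately.

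It can also be said that error terms and contrast families belong in a full protocol or analysis plan that is not shown. That would answer a missing detail. Here the article names a specific procedure as the one that identifies differences. Even on its best reading, that procedure gives no follow-up between the groups and is untouched by the sphericity correction.

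**Conclusion.** The point holds in a limited form. Tukey is a poor choice of named follow-up for this design: it is sound for visits within a group under sphericity, empty for two groups, and unable to test the difference in change. If it were run over all six means with one error term, which the text allows but does not prescribe, the damage would be modest to severe depending on the visit correlation. Power for a 0.7 SD within-woman change would be 3 to 11% with the pooled error, or false group differences would occur in 5 to 32% of trials with the within-woman error. These are alternative harms, not joint ones.

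The figures assume 14 and 13 women, equal visit correlations of 0.3 to 0.8 and a common SD. The point concerns the repeated measures branch only. The wording should be changed before analysis.

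**What to change.** Remove the Tukey step from the repeated measures branch and put in its place:

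> The time-group interaction will be followed by contrasts of the between-group difference in change from baseline at the final assessment and at re-assessment, each with its own standard error, a Holm adjustment and a 95% CI. Intra-group changes will be tested with paired (within-woman) contrasts, also Holm-adjusted.

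The cost is one or two sentences of analysis text, with no new data or participants. The downside is some power for the three visit comparisons within a group. If Bonferroni is used, paired contrasts fall about 5 to 11 points below a correctly specified three-visit Tukey: 69 − 58 = 11, 83 − 73 = 10 and 95 − 90 = 5 at ρ = 0.6, 0.7 and 0.8. Holm is never less powerful than Bonferroni, so it loses no more than this.

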**Fig 7 pone.0308701.g007:**
[figure not shown]
Assessment and re-assessment items. **Note:** ICIQ-SF—International Consultation on Incontinence Questionnaire; ICIQ-OAB—International Consultation on Incontinence Questionnaire Overactive; PFDI -20—Pelvic Floor Distress Inventory; WHOQOL-bref—World Health Organization Quality of Life; FSFI—Function Sexual Female Index; PGI-C—Patient Global Impression of Change.

The primary outcome will be PFM pressure measured by vaginal manometry. Secondary outcomes will include manual muscle strength testing (Modified Oxford Scale) and questionnaires: International Consultation on Incontinence Questionnaire—Short Form (ICIQ-SF), International Consultation on Incontinence Questionnaire Overactive (ICIQ-OAB), Pelvic Floor Distress Inventory (PFDI-20), World Health Organization Quality of Life (WHOQOL), Female Sexual Function Index (FSFI), and Patient Global Impression of Change (PGI-C).

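### The analysis names no deciding contrast for manometry pressure and does not adjust for baseline; one baseline-adjusted between-group difference should be made primary

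*Protocol article*

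**What the plan says.** - **Outcome and visits (Results).** "The primary outcome will be PFM pressure measured by vaginal manometry". No time point is attached. Assessments take place before treatment, at its end and one month after the last session.
- **Analysis (Statistical analysis).** Depending on normality, repeated measures ANOVA or a Kruskal-Wallis test is used, followed by Tukey comparisons. Then: "Time-group interaction and intra-group variations for studied variables will be analyzed". Neither is ranked above the other. No covariate is named. Apart from being one of the visits, baseline values have one stated use: "To assess initial group differences, unpaired t-test or Mann-Whitney test will be used for continuous variables".
- **Sizing (Sample size).** The G*Power procedure is given as "F-tests—ANOVA: repeated measures, between groups", with "significance level of 0.05, power of 98%, and effect size of 0.23"; "the sample size resulted in 27 participants", raised to 32 for losses.

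**The concern.** Three different quantities are in play: the between-groups effect (sizing), the time-group interaction (analysis) and the change within each arm (analysis). They answer different questions and can disagree. Nothing in the article says which one would make the trial positive, or at which visit.

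Each has a weakness as the deciding result:
- The between-groups effect is diluted by a visit at which randomisation makes the expected difference zero.
- The interaction says that the arms' profiles differ somewhere, but gives no single treatment difference in cmH2O with an interval.
- The within-arm changes do not use the control group at all.

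In a trial of 32 women, some chance imbalance in baseline pressure is to be expected. A test of initial differences does not correct for it; a covariate does.

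**Working it through.** **Inputs from the article:** three visits; two arms, 1:1; alpha 0.05; effect size 0.23; power 98%; N = 27 before losses (13 per arm when halved and rounded down), 32 randomised. **Not in the article, so assumed:** between-visit correlation rho (0.3 to 0.8, equal between all visits), a true difference of 0.8 SD, and its time course.

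**1. The plan's own figure.** For the between-groups test, lambda = f²·N·m / (1 + (m−1)·rho), with 1 and N−2 df. With f = 0.23, N = 27, m = 3 and rho = 0, lambda = 0.0529 × 27 × 3 = 4.28 and power is 0.51; at rho = 0.8 it is 0.24. Reaching 98% needs N = 104 (rho 0) to 266 (rho 0.8). The stated 27 is therefore not reproduced from the named test with 0.23 read as Cohen's f. It does appear for the within-between interaction, lambda = f²·N·m / (1−rho), if rho is about 0.79 with three visits or 0.84 with two. Reading 0.23 as f² with rho = 0 in the between-groups test gives 26. So the article leaves unclear which term was powered.

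**2. Dilution of the between-groups effect.** If the difference is 0 at baseline and δ at both follow-ups, the average over visits is (0 + δ + δ)/3 = 2δ/3.

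**3. What baseline adjustment does to the variance.** In units of SD²·(1/n₁ + 1/n₂):
- change from baseline to one follow-up: 2(1−rho)
- ANCOVA at that follow-up: 1−rho²
- ratio, ANCOVA to change: (1+rho)/2, which is 0.65, 0.75, 0.85 and 0.90 at rho 0.3, 0.5, 0.7 and 0.8
- ANCOVA on the mean of both follow-ups: (1+rho)/2 − rho², for example 0.75 − 0.25 = 0.50 at rho 0.5, against 1 − 0.25 = 0.75 for one follow-up

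**4. Power by simulation**, 13 per arm, 0.8 SD at both follow-ups, two-sided 5%:

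| rho | Interaction (2 df) | ANCOVA, end of treatment | ANCOVA, mean of follow-ups |
|---|---|---|---|
| 0.3 | 38% | 51% | 71% |
| 0.5 | 52% | 61% | 77% |
| 0.7 | 76% | 77% | 90% |
| 0.8 | 91% | 90% | 96% |

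The between-groups effect has about 34% at rho 0.5. All these tests hold close to 5% under the null.

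**5. Other time courses**, interaction against end-of-treatment ANCOVA, 13 per arm:
- Effect halves by one month: 39% against 59% (rho 0.5); 63% against 77% (rho 0.7).
- Effect grows to 1.0 SD by one month: 65% against 62% (rho 0.5); 86% against 76% (rho 0.7).

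**6. The Kruskal-Wallis fallback.** This is a one-way rank test for independent groups. It has no interaction term and does not handle repeated measurements on the same woman, so under non-normality the interaction listed in the plan has no test.

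**7. Why unranked within-arm tests matter.** Suppose both arms improve equally, by an assumed 0.5 SD. With 13 to 16 per arm and rho 0.5 to 0.7, the chance that the training arm's change is significant and the comparator's is not is 22% to 25%, although training adds nothing.

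**The case against.** **The plan already has a sound between-group test.** The interaction compares the arms on their changes from baseline, so baseline pressure is taken into account, though less efficiently than by ANCOVA. This stands. A reader might infer that efficacy will rest on within-arm improvement; the article nowhere says so. The defect is the missing ranking, and the 22% to 25% shows only what that leaves open.

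**The between-groups effect is not named as an efficacy test.** It appears in the G*Power label, not in the Statistical analysis section, although a repeated measures ANOVA would print it. This also stands. A reader might set its 34% against ANCOVA as the gain from the fix; the fair comparator is the interaction.

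**The power gain is not guaranteed.** Correct: single-visit ANCOVA gains nothing at rho 0.7 to 0.8 with a sustained effect and loses if the effect grows. The documents give neither rho nor the time course. Nor should the gain be read as a rho² cut in variance: that holds against an unadjusted end-of-treatment comparison, which the plan does not name.

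**A covariate and a primary time point could sit in an unseen analysis plan.** In part. But the article does fix a model, lists two unranked results and sizes on a third, and that mismatch is on the page. That baseline is a level of the time factor is inferred from the three assessments and the model, not stated in words; it is the ordinary reading.

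**Conclusion.** The point holds as a worthwhile improvement, not as a finding that the planned test is invalid. The article names no deciding contrast or time point, sizes the trial on a term other than those it lists for analysis, and leaves baseline pressure out as a covariate.

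The firm benefits are a single interpretable estimate in cmH2O and less variance than change from baseline, by the factor (1+rho)/2 apart from one degree of freedom. The gain over the interaction depends on assumptions. For a sustained 0.8 SD effect with 13 per arm, end-of-treatment ANCOVA runs from 13 percentage points better at rho 0.3 to 1 point worse at rho 0.8. ANCOVA on the mean of both follow-ups is better across that range, by 33 points at rho 0.3 and 5 at rho 0.8. Equal correlation between visits is assumed throughout.

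**What to change.** - Name one primary contrast: the between-group difference in post-treatment manometry pressure, adjusted for baseline pressure, with a 95% CI, tested at two-sided 5%. ANCOVA, or a longitudinal model with baseline as covariate, will serve.
- The sponsor should name the time point: end of treatment, or the mean of both follow-ups if a sustained effect is the question. Other follow-up results become secondary.
- Report intra-group changes descriptively, not as evidence of efficacy.
- Restate the power for that contrast, giving the assumed difference in cmH2O, the SD and rho.

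**Cost.** The analysis change is wording only: no extra visit, measurement or participant. The power statement is more than wording. Under the assumed 0.8 SD with 13 per arm, end-of-treatment ANCOVA has 51% to 90% power over rho 0.3 to 0.8, against the stated 98%. The fix does not repair the sample size; it gives the recalculation a definite target.

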**Methods:**

This study will be a randomized, controlled, parallel, and blinded clinical trial. The final sample will consist of 32 women diagnosed with SUI and cystocele (stage I and II). All volunteers will be assessed and reassessed using the same protocol: assessment form, gynecological examination, functional evaluation of PFM, and questionnaires to assess quality of life, urinary function, and sexual function. All volunteers will be evaluated for satisfaction levels post-treatment. The intervention will be PFMT, totaling 16 sessions to be conducted twice a week. Reevaluation will take place at the end of treatment and 1 month after completion of PFMT. Descriptive analysis and repeated measures ANOVA will be used for result analysis. A significance level of p<0.05 will be considered for all statistical tests.

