### Eligibility criteria

Women with stress urinary incontinence (SUI), identified using the International Consultation on Incontinence Questionnaire—Short Form (ICIQ-SF), and a diagnosis of cystocele at stage I and II according to the Pelvic Organ Prolapse Quantification System (POP-Q) scale [34, 35] will be recruited. The participants’ age range will be between 18 and 65 years, not in menopause, and without a history of gynecological surgeries related to SUI, POP, or hysterectomy. Patients lacking cognitive capacity to comprehend and respond to the questionnaires as determined by the assessor, those with vaginal bleeding, current diagnosis of urinary tract infection, neoplasms, and/or those who decide not to continue participating in the study or withdraw their consent will be excluded.

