### Adverse effects

Adverse effects of PFMT are rare. Any discomfort or pain linked to treatment will be assessed. Volunteers will be closely monitored, asked about session discomfort, and adverse events documented. If risks arise, interventions halt. Withdrawn participants still factor into intention-to-treat analysis.

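### As written, the repeated-measures ANOVA keeps by default only women with all three assessments, which conflicts with the promise that withdrawn women count in the intention-to-treat analysis

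*Protocol article*

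**What the plan says.** - **Method.** The abstract states "Descriptive analysis and repeated measures ANOVA will be used for result analysis". Statistical analysis gives the detail: "Depending on data normality, repeated measures ANOVA or Kruskal-Wallis test followed by Tukey post-test will identify differences", then "Mauchly test will check sphericity, and if violated, Greenhouse-Geisser correction will be applied". The software is fixed: "Data will be analyzed using the Statistical Package for Social Science (SPSS) version 22.0". That section mentions no mixed model, imputation or other handling of a missed visit.
- **Visits.** Under Results: "The assessments will take place at three time points: before treatment (baseline assessment), at the end (final assessment), and one month after the last session".
- **Losses.** Under Sample size: "An additional 20% for possible losses (5 volunteers) was added". This takes 27 to 32, in two groups of 16.
- **Population.** Under Adverse effects: "Withdrawn participants still factor into intention-to-treat analysis".
- **Withdrawals, a second statement.** Under Eligibility criteria: "those who decide not to continue participating in the study or withdraw their consent will be excluded".

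**The concern.** Mauchly's test and the Greenhouse-Geisser correction belong to the classical repeated-measures ANOVA, in which each woman is one row with one column per visit. By default that procedure drops a row with any empty column. A woman who misses only the one-month visit then also loses her baseline and end-of-treatment pressures from the primary test. The result is a completers analysis, although the article promises intention-to-treat.

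The Kruskal-Wallis alternative is no remedy. It does not handle repeated measures, and a woman with no value at a visit cannot enter a test of that visit.

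What is at stake is mainly validity. Under Interventions, one arm attends 16 sessions and the other a single informational visit, so loss that differs by arm or by response is plausible. The contradiction between Eligibility criteria and Adverse effects also leaves it open whether women who stop belong to the analysis set at all.

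**Working it through.** **Inputs.** From the article: 3 assessments; 27 women before losses; 5 added; 32 randomised; alpha 0.05; effect size 0.23, read here as Cohen's f. The correlation between visits is not given and is assumed below.

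**1. The plan's own loss step.** 27 × 0.20 = 5.4, taken as 5, and 27 + 5 = 32. This reproduces. As a share of those randomised, 5/32 = 15.6%.

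**2. Women left in a complete-case ANOVA.**

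| Loss pattern | Calculation | Women left |
|---|---|---|
| The 5 budgeted losses | 32 − 5 | 27 |
| 20% of those randomised (assumption) | 32 × 0.8 = 25.6 | 25 to 26 |
| 20% independently miss each follow-up visit (assumption) | 32 × 0.8 × 0.8 = 20.5 | about 20 |

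So 5 women leave under the plan's own allowance, and up to 12 under the harsher assumption.

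**3. Effect on power.** For the group-by-time test, λ = f²·N·m/(1 − ρ) with m = 3, and degrees of freedom (m − 1) and (N − 2)(m − 1). At f = 0.23 this test gives 27 women for 98% power only near ρ = 0.79, so that value is used first.
- N = 32: λ = 0.0529 × 32 × 3 / 0.21 = 24.18, power 0.994.
- N = 27: λ = 0.0529 × 27 × 3 / 0.21 = 20.40, power 0.982.
- N = 25: power 0.972. N = 20: power 0.926.

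With weaker correlation, the step from 32 to 27 costs more: 0.958 to 0.917 at ρ = 0.7, and 0.801 to 0.721 at ρ = 0.5. These gaps are upper bounds on what a mixed model could recover, because a woman with only a baseline value adds little to the treatment contrast. (The between-groups procedure named under Sample size does not give 27 at f = 0.23. That is a separate matter and does not affect this point.)

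**4. Illustration of bias (all inputs assumed).** The true difference in change is 0.80 SD at both follow-ups, and all visits are equally correlated. Women are lost after the end-of-treatment visit, so only the one-month value is missing. The simulation uses 600,000 per arm so that random error is negligible. Response-dependent loss has logit −1.6 − 1.2 × (end-of-treatment value − centre).

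| Loss mechanism | ρ | Complete-case difference, end of treatment |
|---|---|---|
| PFMT arm: depends on response (centre = arm mean, 22% lost); comparator: 20% at random | 0.5 | 0.91 |
| Same | 0.79 | 0.85 |
| Both arms: depends on response, each centred on its own mean (22% lost in each) | 0.5 and 0.79 | 0.80 |
| Both arms: depends on the absolute value (centre 0.4; 29% comparator and 16% PFMT lost) | 0.5 | 0.74 |

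In the first three rows a likelihood-type estimate using all available values gave 0.80. At one month the complete-case difference was 0.80 in every row, because equal correlations make the change from baseline to one month unrelated to the end-of-treatment value. The bias thus arises where collected end-of-treatment data are thrown away, and its direction depends on the mechanism.

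**5. The two statements on withdrawals.** Eligibility criteria removes women who discontinue or withdraw consent. Adverse effects keeps withdrawn women in the analysis. For a woman who stops attending, both cannot hold.

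**The case against.** The strongest reply is that nothing in the article says incomplete cases will be dropped. Listwise deletion is inferred from the default behaviour of the procedure. Imputation before the ANOVA would make it compatible with intention-to-treat, and an article often leaves missing-data handling to a fuller document. Also, the sentence on withdrawn women follows one about halting the intervention, so it may mean women who stop treatment but are still assessed. They would stay in the ANOVA.

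This stands to the extent that a reader might infer that the ANOVA cannot deliver intention-to-treat. The documents do not support that. They support only that the method as written does not do so by default for a woman with a missed visit. What remains is more than an omitted detail, because the article itself fixes both the method and the population, and its own text on exclusions points away from keeping women who stop.

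Two further readings go too far:
- That 20% losses are expected and leave 26 women. The article speaks of possible losses and counts 5, which is 15.6% of 32 and leaves 27, its own pre-loss number.
- That the completers analysis is necessarily biased. The documents say nothing about why women would be lost, and the illustration shows overstatement, no bias or understatement depending on the mechanism.

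A mixed model restricted to women with at least one follow-up value would itself leave out some randomised women, so the fix has to avoid that restriction.

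**Conclusion.** The point holds in this form: the named ANOVA by default confines the primary test to women with all three assessments, which does not match the stated intention-to-treat analysis, and the article contradicts itself on women who withdraw. Under the plan's own allowance 5 of 32 women leave and 27 remain. The loss of power is small if ρ is near 0.79 and moderate if it is nearer 0.5.

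The more important consequence is possible bias in the end-of-treatment comparison, 0.05 to 0.11 SD on a true 0.80 SD in the least favourable illustration. That size rests wholly on assumed inputs. The conclusion also assumes that no fuller document specifies imputation before the ANOVA. It is a point that should be fixed, not a fatal one.

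**What to change.** 1. Make the primary analysis a linear mixed model for repeated measures in SPSS MIXED: REML, unstructured covariance over the three visits, Satterthwaite degrees of freedom, with group, visit and group-by-visit effects and all available manometry values. Keep baseline in the outcome vector with a mean common to both arms, so that group effects enter only at the two follow-up visits. Every randomised woman with a baseline value then contributes. The sphericity pre-test is no longer needed.
2. Add one pre-specified sensitivity analysis for data not missing at random, for example a delta adjustment of missing PFMT-arm values over a stated range.
3. Reconcile Eligibility criteria with Adverse effects. For the analysis set, women who stop treatment should remain, with the data they have consented to provide.

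If the ANOVA is kept, imputation before it must be specified; that would also resolve the conflict.

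Cost: wording and slightly more analysis work, with no extra women or visits. The mixed model relies on missing at random, which the sensitivity analysis is there to probe. The change should be settled before unblinded data are analysed.
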